**OBJECTIVES**

- 1. To design a package containing linked elements of disease recognition, health communication, treatment, and referral (Triage-Plus) for TB and HIV which:

1. can be adapted for use by a variety of community-based health-care providers
2. strengthens existing community health care networks
3. promotes synergistic and effective linkages with the formal public health service
4. relieves formal public health services from tasks that can be done by the community
5. provides a point of entry for HIV treatment and prevention services
6. builds on different patient perspectives to maintain and strengthen the package
   1. To document processes of the implementation of the Triage-Plus package
   2. To assess the effectiveness and cost-effectiveness of Triage-Plus delivery by different kinds of informal healthcare providers in terms of favourable treatment outcomes for TB and TB and HIV integration.
   3. To build the capacity of the community to improve TB and HIV service delivery at primary health care level
   4. To disseminate the findings to policy makers with a view to inform them on what worked well and how to replicate in other areas across the country

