**Project indicators**

Effectiveness will be measured by comparing quantitative health impact indicators for TB and HIV over the implementation period of Triage-Plus. The demographic and health survey (DHS) report of 2004 used the following defining characteristics and impact indicators: basic population; age composition and structure; gender, level of education, TB, HIV and poverty prevalence. Other indicators will be the number of cases identified, the proportion of cases put on single treatment and the proportion cases put on dual treatment. The same impact indicators will be measured in this study at baseline and on- going till the end of the project in both clusters (i.e. where Triage-Plus is and is not implemented). In this way the intervention is both historically and concurrently controlled.

There is a strong recognition that Triage-Plus is, however, a health system intervention, not a new drug. Therefore the methodology incorporates adaptations and additions to the clinical trial approach such as health economics and qualitative process evaluation. The former to analyse the cost effectiveness of the intervention to patients, informal healthcare providers and the formal health system and the latter to document the multiple changes, processes and to provide the context for the trial findings. In addition, an overarching strategy for the whole research process will be continuous involvement of the research partners, participation of the communities involved in the research, and engagement of those who need and will use the research results.

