With a decision to use six large clusters with at least 166,000 population to minimise pollution of the intervention, a proper sample size calculation using simulations will be implemented to guide the analysis plan. The simulation studies will be carried out before the analysis of the study.

*Data collection tools*

Data collection tools for primary and secondary outcome measures

Prior and subsequent to the intervention, the chronic cough registers, TB treatment registers, HTC and ARV Treatment Registers from health facilities in the whole of Lilongwe District (rural and urban) will be audited for patient numbers by health centre catchment area. These data will form the basis for the trial analysis. Place of residence data are crucially important in this study, so that the study staff can locate patients to traditional authorities and health centre catchment areas that are identifiable within either the intervention or the control area. The study staff will, therefore, conduct initial training and continuing quality assurance checks on these registers throughout the study.

Data collection tools for health economic evaluation

A questionnaire survey will be carried out on a random sample of 166 rural new smear positive TB patients (83 at each site) who have registered for treatment (or both) and 200 rural patients who have recently (within last 2 months) registered for ART at the beginning of the intervention and at the end of the trial period. A patient who has both started treatment for smear positive TB and who is registered for ART will count for both samples, therefore the total sample size may be less than 366. These surveys will capture HIV and TB patients’ pathways to care and collect data on individuals’ household assets and on health-seeking experiences around current symptoms, identifying where and why care was sought (appendix 4). Using a cost-effectiveness check-list data will be collected on staff, consumables, transport and other costs incurred by the health service in this intervention.

Data collection for process evaluation

Throughout the duration of the project, detailed monthly reports will be compiled and all minutes will be recorded. All individuals and organisations involved, their roles and their processes of engagement will be documented. Key informant interviews. Semi-structured interviews and in-depth interviews will also be done.

*Data analysis*

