As an action research, there will be need to collect information of good quality so that the findings give comprehensive understanding of the project activities and findings. To ensure good quality information, the messages for health communication will be pilot tested and feedback will be incorporated in the manual and other training materials that will be developed. There will also be periodic follow-up interviews with members from informal healthcare providers, patients and members of the general community to check quality of information that is being disseminated in the project area.

*Potential benefits*

The community is expected to benefit from the intervention through development of their skills in delivery of services to their clients. There will also be attainment of new skill in areas of referral of TB suspects and HIV cases. New skills will also be gained in areas of disease recognition and care and support of TB and HIV infected people and well as AIDS patients. Members of the community that will be involved in the project will benefit by getting recognition from the community that they will be serving. Above everything else, the community will benefit from being linked up with the formal health service providers. The general community will benefit through awareness of advantages of accessing formal health systems medical services.

The project stands to benefit the patients that would be diagnosed during the project in the intervention area. Among others there will be increased access to good quality information and services. There will also be reduced costs to accessing TB and HIV related services as these services will be brought to the communities. There will also be increased support network within the community as various informal healthcare providers will be brought together to implement the project.

The benefit of the project will also extend to the formal health services providers. The health workers will relieved of work burden as some of the duties of HSAs such follow up of patients and contact tracing will be done by the volunteers from the different informal healthcare providers. The model will provide options for reaching targets for treatment ie TB cure rate, number of people starting on ART and treatment adherence for both TB and ART. Since both TB and HIV programmes are striving to integrate their activities at community level, the model will provide an opportunity of integrating the TB and HIV programmes at community level.

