| 305 | Who decided that you should go there? |  | 1. Self 2. Spouse 3. Household head 4. Relatives/friends 5. Employer 6. Storekeeper referred 7. Referral health worker 8. Othersp:_______   99. Not known | DECIDE |  |  |  |  |  |  |  |  |  |  |
| 306 | a) Did you go there with a guardian? | *If No go to 307* | 1.Yes  2.No |  |  |  |  |  |  |  |  |  |  |  |
|  | b**)** If yes specify the sex of the guardian |  |  | GUARD1 |  |  |  |  |  |  |  |  |  |  |
| 1.Male  2.Female |  |  |
| 307 | How much did you spend (on drugs, fees, consultation)? | *Fill in for each visit to the care provider* | MK | FEES1 | MK | MK | MK | MK | MK | MK | MK | MK | MK | MK |
| 308 | How did you get the money? |  | 1.Own money  2. From Spouse  3.From children/parents  4.From friends/relatives  5.Borrowed (without interest)  6.Borrowed (with interest)  7.Begging  8.Sold assets  9.Othersp:__________ | MONEYHOS |  |  |  |  |  |  |  |  |  |  |

|  |  |  |  |  | 1st | 2nd | 3rd | 4th | 5th | 6th | 7th | 8th | 9th | 10th |
| --- | --- | --- | --- | --- | --- | --- | --- | --- | --- | --- | --- | --- | --- | --- |
| 309 | How did you travel? |  | 1. Did not travel | TPTMODE1 |  |  |  |  |  |  |  |  |  |  |
| 2. Walk | TPTMODE2 |  |  |  |  |  |  |  |  |  |  |
| 3. Bus/Minibus | TPTMODE3 |  |  |  |  |  |  |  |  |  |  |
| 4. Ambulance | TPTMODE4 |  |  |  |  |  |  |  |  |  |  |
| 5 Bicycle | TPTMODE5 |  |  |  |  |  |  |  |  |  |  |
| 6 Own car | TPTMODE6 |  |  |  |  |  |  |  |  |  |  |
| 7 Hired car/Taxi/bicycle | TPTMODE7 |  |  |  |  |  |  |  |  |  |  |
| 8. Stretcher | TPTMODE8 |  |  |  |  |  |  |  |  |  |  |
| 9. Wheel barrow/Oxcart | TPTMODE9 |  |  |  |  |  |  |  |  |  |  |
| 10. Other sp: | TPTMODE10 |  |  |  |  |  |  |  |  |  |  |
| 99. Not Known |  |  |  |  |  |  |  |  |  |  |  |
| 310 | How much did you pay for transport (going there and back including for guardian(s))? | *Fill in for each visit to the care provider*  *(if answer is 2 above then skip this question)* | MK | TPTCOST1 | MK | MK | MK | MK | MK | MK | MK | MK | MK | MK |
| 311 | How much time did you take to go and come back (hrs)? | *Fill in for each visit to the care provider* | Hours | TIME1 | HRS | HRS | HRS | HRS | HRS | HRS | HRS | HRS | HRS | HRS |
| 312 | How much did you spend on food and incidentals? | *Fill in for each visit to the care provider* | MK | FOODFEE1 | MK | MK | MK | MK | MK | MK | MK | MK | MK | MK |

|  |  | | |  | |  | |  | 1st | 2nd | 3rd | 4th | 5th | 6th | 7th | 8th | 9th | 10th | |

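### The economic analysis promises a perspective that includes informal healthcare providers, but no named tool collects the time or expenses of providers outside the health service

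*Protocol*

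**What the plan says.** The Objectives section of the protocol includes this aim: "To assess the effectiveness and cost-effectiveness of Triage-Plus delivery by different kinds of informal healthcare providers". Project indicators then states whose costs and benefits the health economics component covers: "The former to analyse the cost effectiveness of the intervention to patients, informal healthcare providers and the formal health system". That is a three-party perspective.

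The Data collection process section names two sources for the economic evaluation:

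- A questionnaire to samples of registered smear-positive TB patients and recently registered ART patients, at the start of the intervention and at the end of the trial. It covers household assets and the pathway to care, "identifying where and why care was sought (appendix 4").
- A check-list: "Using a cost-effectiveness check-list data will be collected on staff, consumables, transport and other costs incurred by the health service in this intervention".

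The process evaluation, described separately, consists of monthly reports, minutes and interviews. On providers it says: "All individuals and organisations involved, their roles and their processes of engagement will be documented".

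Under Ethical considerations, among the potential benefits, the protocol expects health workers' load to fall because some "duties of HSAs such follow up of patients and contact tracing will be done by the volunteers".

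**The concern.** The perspective is stated in one place and the data that would support it are fixed in another, and the two differ by one party. The missing party is the one whose work the package is designed to increase. Besides the HSA duties that pass to volunteers, Table 1 gives informal providers community sputum collection and transport, treatment supervision and referral.

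Two things are at stake. First, part of a stated objective would lack data. Second, work that leaves paid health staff would drop out of the health-service count and reappear nowhere, which tilts the economic comparison towards the intervention. The Objectives section intends the findings to tell policy makers how to replicate the model elsewhere, and what the model asks of unpaid providers bears directly on that.

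**Working it through.** The protocol gives no figure to reproduce. The check matches each party in the stated perspective to the tools that could supply its costs, then asks which way any gap would push the result.

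**1. Patients: covered.** Appendix 4 asks about the patient's own outlay ("How much did you spend (on drugs, fees, consultation") in item 307. It also covers transport, including guardians (310), travel time (311), food and incidentals (312), the total per provider visited (314) and working days lost (401 and 402).

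**2. Formal health system: covered.** The check-list takes in staff, consumables, transport and other costs. All of these, including the other costs, are qualified as those of the health service.

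**3. Informal healthcare providers: partly covered.** The protocol uses this term for two kinds of provider.

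- *HSAs, nurse midwives and auxiliary antenatal nurses.* The Intervention package section lists them as primary health care providers. They work within the health service, so the check-list's staff costs can include their time.
- *Storekeepers, home-based care and community groups, and volunteers.* They are not health-service staff. Health-service spending on their training or supplies could reach the check-list. Their own time and expenses could not.

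**4. Other tools that might fill the gap.**

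- Appendix 4 is answered by patients and has no item on a provider's hours or costs.
- Appendix 3, the capacity topic guide, asks how a group was formed, its affiliations, its funding (including monetary and in-kind contributions) and its composition. It asks about sources of support, not about what members spend or how long they work.
- The process evaluation names roles and engagement. The content of the monthly reports is not itemised, so they might hold hours, but nothing in the protocol requires it.
- Interviews and focus groups are planned, but no cost or time topic is named for them.

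**5. Direction of the effect.** Write the incremental cost of the intervention as

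ΔC = ΔC(patients) + ΔC(health service) + ΔC(outside providers).

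The named sources supply the first two terms. When a task such as contact tracing moves from an HSA to a volunteer, ΔC(health service) falls by the value of the HSA time released. ΔC(outside providers) rises by the value of the volunteer time used plus expenses. If only the first two terms are measured, the fall is counted and the rise is not, so incremental cost is understated by ΔC(outside providers). This favours the intervention whenever that term is positive. It should be positive where volunteers take on additional work, and it arises mainly in the clusters where Triage-Plus is running.

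**6. Size.** ΔC(outside providers) equals (number of providers) × (additional hours each) × (value per hour) + own expenses. The protocol gives none of these four inputs, so no magnitude can be derived from it.

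**The case against.** The strongest reply is that the check-list is named but not reproduced, the two sources are not said to be exhaustive, and itemised costing and the valuation of volunteer time are commonly left to a later analysis plan. Valuation can indeed wait. Collection cannot: the protocol itself sets the check-list's scope as health-service costs, and provider hours not logged during delivery are hard to recover afterwards.

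A second reply is that the extra burden is presumed. The literature review section says providers will carry out these tasks within their daily routine, and home-based care groups already look after chronically ill people. This stands as a caution about size, since how much volunteer time is additional is unknown. It does not show that the amount is nil, because the protocol explicitly expects that "contact tracing will be done by the volunteers from the different informal healthcare providers".

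A third reply is that HSAs and antenatal nurses count as informal providers and can be costed as health-service staff. This stands, and it makes the gap partial.

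A reader might also infer that the protocol fixes a biased cost per additional treatment start, with volunteer time valued at nothing. The documents do not support that. Cost-effectiveness is an objective and an analysis component, not a defined endpoint. No such ratio appears, and Objectives ties the assessment to favourable treatment outcomes and TB and HIV integration. No valuation rule for volunteer time is stated either. What is established is that no tool is named to collect the data.

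**Conclusion.** The inconsistency is real and lies in the protocol's own text. Project indicators names three parties, while the data collection section provides fully for two and partly for the third. As written, the provider part of the stated perspective cannot be fully assessed, and work shifted from HSAs to volunteers would probably make the intervention look cheaper.

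The direction rests on two assumptions: that volunteers do some additional work under Triage-Plus, and that no unlisted tool records it. Any figure for uncosted hours or money would rest on invented provider numbers.

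It would go too far to say that the provider question is beyond answering, since the health-service part of that group can be costed. It would also be wrong to extend the point to the main trial result: the two primary outcomes, TB treatment starts and ART starts, do not depend on cost data. The point deserves correction because a stated objective is only partly supported and the remedy is cheap.

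**What to change.** Choose one of two changes.

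- **Collect the data.** In the section on data collection tools for the health economic evaluation, extend the check-list, or the monthly reports already planned, to record hours spent on Triage-Plus tasks and own expenses. Do this for informal providers outside the health service in the clusters delivering the package. State that HSAs and antenatal nurses are counted once, as health service, so that their time is neither missed nor counted twice.
- **Narrow the claim.** Remove informal healthcare providers from the perspective in Project indicators, and state that volunteer costs are excluded, so that policy readers can see the limit.

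The first option costs a small reporting burden on providers and may give a less favourable cost-effectiveness result. The second costs only a wording change, but gives up part of what the protocol set out to examine.

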**Mobilisation of community and monitoring of project activities**

The entry point in the communities will be local leaders (village headmen and traditional authorities) and health surveillance assistants (HSAs). These are people who the community recognise as opinion leaders. The opinion leaders will be advised on the need for close consultation amongst themselves when mobilising the community or organising any activity. The structures that these people use to mobilise the people will be used to mobilise the communities. The community members will be involved in the development of the IEC materials. This will be done to ensure that the message is clear and is culturally acceptable by the community. Pre-testing of the messages will be also be done with the community to check the meaning and acceptability from the community’s perspective.

The district health office (DHO) will be playing advisory role during implementation of the project. Staff from the DHO will form part of facilitating team during training of informal healthcare providers. Since the intervention activities will be taking place in the DHOs area of jurisdiction, the officers will be involved at every step of the project development and implementation. As such, the HSAs at every health facility will be supporting REACH Trust staff in monitoring the project activities in the health facility catchment area.

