**Project site**

The project will be implemented in rural parts of Lilongwe district. Ideally, the study region would be divided into “clusters”, each consisting of geographically delineated area (defined by a combination of at least 2 traditional authorities). The clusters would then be randomised to either receive the intervention (Early intervention arm) or to act as a control, (Delayed intervention arm) using stratification methods to ensure that the two sets of clusters would be as similar as possible in terms of their poverty profile, population structure, health service coverage, and presence of significant number of at least one of the selected community-based health care providers (store-keepers, ante-natal care clinic and home-based care organisations).

The problem with this methodology is that people in the study clusters do not always attend their “local” health centre, so there would be considerable problems of “pollution” between the two study groups, in that people living in intervention clusters would attend control cluster health centres, and vice versa. While it would be technically relatively simple to identify the location of participants’ homes (and hence do an “intention-to-treat” analysis with individuals assessed according to their actual residence address rather than health centre attended), this would not eliminate the likelihood that some people resident in control clusters would be exposed to the intervention and some people resident in intervention clusters would not be exposed to it. The decision was thus taken to divide the rural parts of Lilongwe district into just six groups with large population sizes of at least 166,000. A random number will be generated in Excel to determine which clusters will receive the intervention early and which will ones will receive the intervention later. Thus, the six study clusters will equally be randomised to the Early intervention arm (to receive the intervention early in the first 12 months) and the Delayed intervention arm (to receive the intervention after 12 months). The 6 clusters will be pair-matched according to population sizes and their proximity to the urban areas.

Because the intervention is to be implemented at community level, allocation of the intervention will not be blinded to the communities and the research team implementing the intervention. However, allocation of TB and HIV cases to the clusters will be blinded.

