**ORGANISATIONAL FACILITIES**

Research for Equity and Community Health (REACH) Trust is an independent research trust in Malawi which has grown out of a long established collaboration between the Malawi National TB Control Programme, the Department of Sociology, University of Malawi and the Liverpool School for Tropical Medicine.

REACH trust conducts multidisciplinary research to promote equity in health care. It is run by the Director and has a staff compliment of 30 which includes; research managers, senior Researchers, Researchers, Research Assistants and Administration and Finance Staff. The research team includes experts in Sociology, Clinical Sciences and Health Economics.

The trust is well equipped with facilities for research work. Every officer has a computer; either laptop or desk top and are also connected to internet to facilitate literature search and relevant information from websites. It has a saver which is also used for backups

The trust uses different updated software such as Epi-Info, statistical package for social scientist (SPSS), STATA which are mainly used for quantitative data analysis. We also use MAXQDA for qualitative analysis.

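### Delivery costs are to be collected as those the health service incurs, which leaves out the project team's and informal providers' shares and tilts the cost-effectiveness ratio in favour of the package

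*Protocol*

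**What the plan says.** Cost-effectiveness is a stated objective (Protocol, Objectives): "To assess the effectiveness and cost-effectiveness of Triage-Plus delivery by different kinds of informal healthcare providers". The findings are to go to policy makers, to "inform them on what worked well and how to replicate in other areas across the country". Project indicators names whose cost-effectiveness is meant; the economic component is "to analyse the cost effectiveness of the intervention to patients, informal healthcare providers and the formal health system".

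The data to support this are described under Data collection process, in the paragraph on tools for the health economic evaluation. There are two sources. One is a questionnaire survey of TB and ART patients (Appendix 4), which records patients' own spending, travel and lost work. The other is a check-list covering "staff, consumables, transport and other costs incurred by the health service in this intervention".

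On who does the work, Project site says that "allocation of the intervention will not be blinded to the communities and the research team implementing the intervention". Under Mobilisation of community and monitoring of project activities, the district health office advises, its staff make up part of the training team, and the health surveillance assistants "will be supporting REACH Trust staff in monitoring the project activities". Organisational facilities says that REACH Trust "is an independent research trust in Malawi", and the section on dissemination names it as the project's institutional host.

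**The concern.** The check-list is defined by payer: it covers what the health service incurs. The protocol's own account has a body outside the health service doing part of the delivery. Followed as written, the trust's and partners' spending on delivery never enters the cost side of the ratio, although its effects enter the other side. Costs falling on informal providers are missing too, despite the promise in Project indicators.

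The objective at stake is replication. A district that takes up the package has to resource provider mapping, materials, training and monitoring, whoever paid for them during the trial. A ratio without the project's share answers a narrower question than the one put to policy makers. One stated aim of the package is to relieve formal services of tasks that the community can do. Health-service cost could therefore fall while the outside resources that make this possible go uncounted.

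**Working it through.** The protocol gives no budget, unit cost or cost-effectiveness ratio, so there is no figure to reproduce. The check sets the passages side by side and then works out the direction of the bias.

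**Who bears which delivery activity, and is it captured?**

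| Activity | Who is named | Captured by the check-list as worded? |
| --- | --- | --- |
| Training of informal providers | District staff as part of the facilitating team (Mobilisation section); health workers (Intervention package) | Health-service share yes; trust's and partners' share no |
| Supervision of informal providers | Health surveillance assistants (Ethical considerations) | Yes |
| Monitoring of activities | REACH Trust staff, supported by health surveillance assistants (Mobilisation section) | Assistants' time yes; trust's time no, where it is delivery rather than research |
| Mapping of providers; development and pre-testing of information materials | Described as project work, with community, health-worker and national expert input (Intervention package) | Health-service input only |
| Informal providers' own time and expenses | Informal providers | No |

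**Is the gap closed elsewhere?** The patient survey measures patients' costs, not delivery costs. The process evaluation records roles, engagement, minutes and monthly reports, not spending. No section says that the trust's, the partners' or the informal providers' costs will be collected.

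**Direction.** Let
- H = extra delivery cost borne by the health service,
- P = delivery cost borne by others (the trust, partners, informal providers),
- E = the gain in effect, taken as positive.

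Full ratio = (H + P)/E. Ratio from the collected data = H/E. The shortfall is P/E, which is above zero whenever P is above zero, even if H is small or negative.

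When H is positive, write s = P/(H + P). Then H/E = (1 - s) × (H + P)/E, so the full ratio is 1/(1 - s) times the reported one.

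**Illustration.** The values of s are assumptions; nothing in the documents supports one over another.

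| s (assumed) | Reported ÷ full = 1 - s | Full ÷ reported = 1/(1 - s) |
| --- | --- | --- |
| 10% | 0.90 | 1/0.90 = 1.11 |
| 25% | 0.75 | 1/0.75 = 1.33 |
| 50% | 0.50 | 1/0.50 = 2.00 |

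**The case against.** The case on the other side has several parts.

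- **The wording states no exclusion.** The check-list is not reproduced. The closing phrase could be read as qualifying only the other costs, leaving staff, consumables and transport open to any payer. The trust's spending also sits in its own accounts and needs no field tool. These readings are possible, but nothing in the text supports them. The only sentence on delivery costs names one payer, and no sentence says the accounts will be used.
- **Much of the work is health-service work.** This stands in part. District staff help to train, health workers help to develop the training materials, mobilisation runs through local leaders and health surveillance assistants, and those assistants supervise the informal providers. A reader might infer that all training, information and supervision spending is costed at zero. The documents do not support that: only the share borne outside the health service is lost. The protocol does not say who pays for each item, and the clause about the implementing team comes from a sentence on blinding.
- **Some trust activity is research.** Monitoring and follow-up interviews may be partly research work, which should stay out of the ratio. This stands, and the fix has to separate the two.
- **Perspective and cost items are often left to an analysis plan.** Fair for detail such as line items. Here, though, the protocol fixes a scope, and that scope is narrower than its own statement in Project indicators.
- **Severity.** Cost-effectiveness does not appear among the abstract's objectives, and no primary outcome, test or effect estimate is touched. This stands and keeps the point at a lower severity.

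**Conclusion.** The point holds in a limited form. As written, cost collection covers the health service's share of delivery and omits whatever the trust, its partners and the informal providers bear. It is also inconsistent with the perspective promised in Project indicators. Any omitted delivery cost makes the package look more cost-effective than it is for a district that must resource all of it.

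The direction rests on two conditions: that some delivery cost falls outside the health service, which the protocol's division of work indicates, and that the effect is positive. The size cannot be computed, because the documents contain no costs; the 1.11 to 2.00 range above only shows how the formula behaves.

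A reader might also go further and divide assumed project spending by the sample-size targets, to express the omission as a cost per extra treatment start. The documents do not support that. The objective states cost-effectiveness in terms of favourable treatment outcomes and TB-HIV integration, not treatment starts, and the targets were set for power.

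**What to change.** In the health economic paragraph of Data collection process, replace the health-service restriction with wording such as: *data will be collected on all resources used to deliver the package, whoever bears them (health service, REACH Trust and partners, informal providers), excluding resources used only for research.*

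- Take the trust's and partners' share from their accounts. Project type already divides the project into an intervention and a research component, so spending can be coded along that line. It is best coded as it occurs, since it is harder to reconstruct later.
- Leave out research-only items such as register audits, surveys and research interviews.
- Add a simple record of informal providers' time and expenses.
- State one perspective, consistent between Objectives, Project indicators and this paragraph.

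Reporting start-up and recurrent costs separately would help a district planning replication, but it is optional.

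The cost is a wording change, some accounting work and a modest extra record from informal providers. The ratio will be less favourable wherever these parties bear delivery costs. Nothing changes in the primary outcomes, sample size or main analysis.
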